**Fig. 1 Fig1:**
[figure not shown]
Location of Dingchuan acupuncture point

The TENS simulated group (control) will have electrostimulators that are the same make and model as the experimental group but that have been modified to have no electrical outlet, even though the screen will light up and display the same data as in the unmodified device. Patients in this group will be informed that, owing to the frequency of stimulation, it is unlikely they will feel the electric stimulation.

In both groups, the session will last 45 min and will take place during a maximum of five consecutive days or until the patient is discharged.

If the acuTENS stimulation produces any kind of discomfort, the intensity of the current being applied to the patient will be reduced. If for any reason a treatment cannot be administered or is administered differently from the original protocol (e.g., only 30 min of treatment because the electrostimulation device had no battery), this will be reported. Any discomfort or skin reaction will be reported as an adverse event.

The interventions will be performed by physiotherapists or physicians who have a minimum of one year of clinical experience and who have been trained in the handling of the two treatment protocols. There will be a pre-pilot test to detect potential problems and ensure the adequacy of the implementation of the protocols.

Adherence to the treatment will be reported. No special stages for improving adherence will be taken since all patients will be hospitalized in the participating centres.

Both groups will receive the standard treatment for patients with AECOPD (bronchodilators, steroids, etc.) in accordance with medical criteria as well as the treatment with acuTENS or simulated acuTENS. No treatment is prohibited.

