#### Secondary outcome measures

Hospitalization length will be measured by using the number of days from the time of admission until the patient’s discharge. Scores will be compared by using mean differences between groups.

Peak expiratory flow will be assessed by using a peak flow meter and using litre per minute units at baseline and after each treatment session. For each assessment, peak flow will be measured three times and only the highest score will be considered. Differences will be assessed between groups by using mean scores at each day (days 1 to 5).

Adverse events will be recorded after each treatment session; the evaluator will ask the patient for any adverse event related to the intervention. Description of each event and its frequency will be described for each group.

Blood gas analysis—partial pressure of oxygen (PaO_2_), partial pressure of carbon dioxide (PaCO_2_), arterial blood pH, bicarbonate and oxygen saturation (SaO_2_)—at days 1 to 5 will be recorded if available in the patient’s clinical history since no specific analysis will be made for the trial. Differences will be assessed by comparing means at each day (days 1 to 5).

Relapse and readmissions at 3 months after discharge will be assessed by using the participant’s clinical history. Mean number of relapses and readmissions during the 3-month period after discharge will be compared between groups.

Mortality will be assessed by using the ratio of patients who died during the 3-month period after discharge in each group.

Quantity of drugs administered during patient’s hospitalization will be extracted from the patient’s clinical history. Mean dosages will be compared between groups. Data will be collected by using a standard form designed by the study investigators, and database entry will be double-checked.

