### Blinding

Trial participants, outcome assessors and usual care providers will be blinded during the trial, and only the physiotherapists who will perform the acuTENS or sham acuTENS procedure will know the patient’s allocation. To ensure that they remain blinded to allocation, the medical staff will not be present during the application of technology. There will be no circumstances under which unblinding is permissible. Data analysis will be performed by a blinded external statistician.

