### Statistical methods

There will be a descriptive analysis of the demographic data by using means and standard deviations (mean ± standard deviation) for continuous variables and absolute values and percentages for qualitative outcomes.

For the comparative analysis between the two groups, continuous outcomes (such as Borg scale score and number of hospitalization days) will be analysed by using mean differences with a 95% confidence interval with a Student *t* test or Mann–Whitney *U* test depending on the distribution of these. For dichotomous outcomes (such as mortality at 3 months), risk ratio will also be used with a confidence interval of 95% and chi-squared test.

The main analysis will be carried out by intention to treat, but there will be another per-protocol analysis for patients who have received at least three interventions. A *P* value of less than 0.05 will be considered significantly different.

In case of missing data, last value carried forward methods will be used. In case of significant baseline differences between the two groups, there will be an adjusted analysis for these outcomes.

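### Blood gases are available only where clinicians chose to draw them, yet arms are compared by daily means; the comparison is not a randomised one and can be biased

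*Protocol article*

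**What the plan says.** In the protocol article, under Secondary outcome measures, PaO2, PaCO2, arterial pH, bicarbonate and SaO2 on days 1 to 5 are taken from the clinical record only where a value exists, "since no specific analysis will be made for the trial". The analysis follows at once: "Differences will be assessed by comparing means at each day (days 1 to 5".

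Statistical methods assigns continuous outcomes a "Student *t* test or Mann–Whitney *U* test depending on the distribution of these", with significance at P below 0.05. It adds "The main analysis will be carried out by intention to treat" and "In case of missing data, last value carried forward methods will be used". No exception is made for gases.

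Two other statements bear on who has a gas value. Under Interventions, sessions "will take place during a maximum of five consecutive days or until the patient is discharged". Under Blinding, "Trial participants, outcome assessors and usual care providers will be blinded during the trial".

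**The concern.** A between-arm comparison is protected by randomisation only if everyone randomised is measured, or if being measured is unrelated to treatment and outcome. Here the treating clinician decides, day by day and after randomisation, whether a gas is taken. A sicker or more breathless patient is plausibly sampled more often, and the treatment is meant to relieve breathlessness. If it does, fewer treated patients may be sampled, and those who are may be the sicker part of their arm. Early discharge removes further patients in the same selective way.

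At stake is the reading of the trial's gas-exchange results. An effective treatment with no influence on gases could appear to worsen them, or a modest improvement could be hidden. The plan states this comparison outright, so the point does not rest on detail left to a fuller document. It concerns 5 measures × 5 days = 25 daily comparisons.

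**Working it through.** **The plan's own figure.** The only sample size in the article is for the Borg score: difference 2, SD 2.6, α 0.05 (two-sided assumed), power 0.80, 10% losses. Per arm, 2 × (1.96 + 0.84)² × 2.6² / 2² = 26.5, rounded up to 27. That gives 54 in total, and 54 / 0.90 = 60, as stated. The figure is not in dispute, but it is not based on gases.

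**Inputs for the bias.** From Sample size: a Borg difference of 2 and an SD of 2.6, so 2 / 2.6 = 0.77 SD. Assumed, because the documents give nothing: no true effect on gases, the rule by which gases are drawn, and the within-arm correlation r between severity and gas value. Bias is in SD of the gas, in the direction that makes acuTENS look worse.

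**Case 1: no bias.** If draws do not depend on severity, or treatment does not change severity, both arms are selected in the same way and the expected difference is 0. Simulation confirmed this to within about 0.003 SD.

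**Case 2: graded draw rule.** The log-odds of a draw rise by 0.5, 1 or 2 per SD of current severity, with about 41 to 44% of controls drawn and severity lowered by 0.77 SD on treatment. The bias is r times the arm difference in mean standardised severity, each measured from its own arm mean, among those drawn:

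| Log-odds per SD | Drawn, acuTENS v control | Severity difference | Bias, r = 0.3 | Bias, r = 0.5 |
|---|---|---|---|---|
| 0.5 | 32% v 41% | 0.041 | 0.01 | 0.02 |
| 1 | 27% v 42% | 0.133 | 0.04 | 0.07 |
| 2 | 23% v 44% | 0.307 | 0.09 | 0.15 |

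At r = 0.6 the last row reaches about 0.19 SD in simulation (0.307 × 0.6 = 0.18).

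**Case 3: hard Borg cut.** Same-day Borg is normal with SD 2.6 and mean 5 (control) or 3 (acuTENS), and a gas is drawn only at or above cut c. With a = (c − mean) / 2.6, the share drawn is 1 − Φ(a), and the mean standardised severity of those drawn is λ(a) = φ(a) / (1 − Φ(a)). The bias is r × [λ(acuTENS) − λ(control)].

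- c = 4: a = 0.385 v −0.385; drawn 35% v 65%; λ = 1.058 v 0.570; difference 0.488; bias 0.15 (r = 0.3) to 0.24 (r = 0.5).
- c = 5: a = 0.769 v 0; drawn 22% v 50%; λ = 1.344 v 0.798; difference 0.546; bias 0.16 to 0.27.

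With 30 per arm, simulated rejection under no true gas effect was about 6.5% to 10% per test, against a nominal 5%.

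**Carry-forward.** Peak flow and Borg have a stated baseline; gases are listed only for days 1 to 5. A patient never sampled has nothing to carry. Under the hard-cut rule, carry-forward lowered the day-5 bias from 0.20 to 0.14 SD when the treatment effect built up over the days and gases had no time trend. It raised the bias from 0.19 to 0.23 SD when the full effect applied and gases had a time trend. It is not a repair, and its direction is not fixed.

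**Precision.** The detectable difference at 80% power is 2.80 × √(2/m) SD for m sampled per arm: 0.76 at m = 27, 1.10 at m = 13 (about half sampled) and 1.40 at m = 8 (about 30%). A daily gas test would have little power even without bias.

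**The case against.** The strongest reply is that bias is possible but not shown. Nothing says that clinicians order gases on the Borg score, which trial evaluators collect. If draws follow gas exchange itself and treatment does not alter gases, treatment does not change who is sampled; simulating that rule gave bias of about 0.00 SD and rejection of 4 to 6%. If the Borg effect builds up from 20% to 100% over five days, even the hard cut gives only 0.03 to 0.08 SD on days 1 and 2. Opportunistic sampling is openly declared, clinicians are blinded, and gases are only one group of secondary outcomes. The phrase about availability might also mean that only available cases are analysed, without carry-forward; the article does not say.

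Much of this stands, and it rules out three readings that a reader might infer:

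- That the gas results will be biased, by a known amount, across all 25 tests. The documents supply none of the quantities needed, and the largest figures need a hard cut and the full 2-point effect on the day in question.
- That carry-forward necessarily adds to the bias. It can go either way.
- That a safety claim against opioids is at stake. The Discussion describes acuTENS as added to usual treatment, Interventions prohibits no treatment, and opioids appear only in the Background.

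The core remains. Blinding prevents draws prompted by knowledge of allocation, but not draws prompted by the patient's response. Declaring the sampling opportunistic does not make the stated comparison of means a randomised one, and neither does the intention-to-treat label.

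**Conclusion.** The point holds in a limited form: the planned daily comparison of blood gases uses a subset selected after randomisation and can be biased. It is valid only if draws are unrelated to whatever the treatment changes, a condition that the plan neither states nor checks. With no true gas effect and r between 0.3 and 0.5, the illustrative bias runs from zero, through about 0.01 to 0.15 SD (graded rule, 2-point Borg effect), to about 0.27 SD at most (hard Borg cut, false-positive rate up to about 10% per test). These are scenarios, not estimates. The primary outcome and the sample size are untouched. The change is worth making because the remedy is cheap and the tests given up have little power.

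**What to change.** - In Secondary outcome measures, replace the daily between-arm comparison of gases with descriptive reporting: values by arm and day, with the number and share of patients sampled by arm and day.
- In Statistical methods, exempt blood gases from last value carried forward.
- If a between-arm gas comparison is kept, limit it to one per gas over days 1 to 5, label it exploratory, and state that sampling was at clinicians' discretion after randomisation.
- Imputation using the daily Borg score and peak flow, both already collected, should be a sensitivity analysis only. With half or more of an arm possibly missing on a day it depends heavily on the model, and it fails if draws follow severity that is not recorded.

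The cost is wording and a small table, with no new blood draws. The drawback is that gas results become descriptive or exploratory.

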## Background

Chronical obstructive pulmonary disease (COPD) is characterized by persistent and progressive airflow limitation associated with a chronic inflammatory response in the airways and lung parenchyma to noxious particles or gases [1]. COPD is a major cause of morbidity and mortality worldwide and its prevalence is expected to increase over the next decade because of continuous exposure to risk factors and the aging of the population [2]. It is estimated that in 2030 COPD will be the fourth leading cause of death globally [3]. Currently, the prevalence of the disease in Spain is 10.2% of the population between 40 and 80 years of age [4].

Dyspnoea, along with chronic cough and sputum production, is one of the main symptoms of COPD. Its severity and magnitude increase as the disease progresses and this disease is the main cause of disability and reduced quality of life in patients with COPD [5].

Patients may experience periods of acute exacerbation of COPD (AECOPD), defined as “a sustained worsening of the patient’s condition, from the stable state and beyond normal day-to-day variations, which is acute in onset and necessitates a change in regular medication in a patient with underlying COPD” [6]. These can be particularly severe exacerbations requiring hospitalization. In Spain, it is estimated that hospitalizations for AECOPD have an average cost of 344.96 euros per person per day [7], most of which is due to stays in hospital. These exacerbations are associated with 12% of mortality and 35% of readmissions up to 3 months after discharge [8].

Treatment of AECOPD includes bronchodilators, corticosteroids, antibiotics, oxygen therapy and non-invasive mechanical ventilation [9]. In the case of severe dyspnoea, oral or parenteral administration of opioids is recommended, although these have side effects and can cause respiratory depression [5]. However, dyspnoea remains a major symptom in patients hospitalized for an AECOPD [7].

The acupoint transcutaneous electrical nerve stimulation (AcuTENS) is a modern technique based on traditional acupuncture. It involves the stimulation of acupuncture points by using transcutaneous electrical nerve stimulation (TENS) instead of needles, which makes it a very-easy-to-learn, non-invasive method without the traditional acupuncture adverse effects such as infections or puncture of internal organs [10].

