### Randomization and allocation

Participants will be randomly assigned to the acuTENS or sham acuTENS group with a 1:1 allocation by using a computer-generated randomization list. A blocked randomization list will be generated for each centre by the main author, who will not be involved in recruitment or assessment. Randomization lists will be kept by using an electronic key and will be available only to the persons responsible for administering the treatments.

Once participants give consent for participation, a consecutive number will be assigned by the head of recruitment, and the staff responsible for administrating the treatment will match the patient’s number with the randomization list to define the patient’s allocation.

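### The 3-month relapse and readmission count takes no account of death, so a patient who dies after discharge without readmission scores zero, the best result (minor, secondary outcome)

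*Protocol article*

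**What the plan says.** The protocol article, under Secondary outcome measures, gives the source of the outcome: "Relapse and readmissions at 3 months after discharge will be assessed by using the participant’s clinical history". It then fixes the summary measure: "Mean number of relapses and readmissions during the 3-month period after discharge will be compared between groups". Death over the same period is a separate secondary outcome: "Mortality will be assessed by using the ratio of patients who died during the 3-month period after discharge in each group".

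Under Statistical methods, continuous outcomes are compared by "mean differences with a 95% confidence interval with a Student" *t* test, or by a Mann–Whitney test, depending on their distribution. On the analysis set it says: "The main analysis will be carried out by intention to treat". The only rule for incomplete data is: "In case of missing data, last value carried forward methods will be used".

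The Background gives the expected frequency of both events: "These exacerbations are associated with 12% of mortality and 35% of readmissions up to 3 months after discharge".

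The article mentions no time at risk, no rule for death in this outcome, and no combination of readmission with death.

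**The concern.** A count over a fixed window measures the tendency to be readmitted only if patients stay at risk for the whole window. Death ends that risk. A patient who dies at home on day 10 has a count of zero and cannot be told apart from a patient who stays well for three months. Patients who die after one readmission also have their count cut short.

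On the protocol's own background figures, death is about one third as frequent as readmission (12/35 = 0.34), so this is not a rare event that can be ignored. If one arm has more deaths, its mean count falls for that reason alone. Conversely, an arm with better survival keeps more frail patients alive to be readmitted, and its count rises. Since the trial sets out to assess both mortality and readmission, the two results should be readable together.

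**Working it through.** **Inputs from the protocol article.** 12% mortality and 35% readmissions up to 3 months (Background); 60 patients (Sample size); 1:1 allocation (Randomization and allocation), hence 30 per arm. The article gives no rate, power or sample size for the readmission outcome, so it states no figure for this outcome that could be reproduced. The total of 60 does reproduce for the Borg outcome: 2 × (1.96 + 0.84)² × 2.6² / 2² = 26.5, so 27 per arm; 27/0.9 = 30 per arm.

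**Assumptions (not in the article).** Readmissions follow a Poisson process with mean rate −ln(1 − 0.35) = 0.431 per 3 months. Death times are uniform over the 3 months. Patients who die have a readmission rate R times that of the others while alive, with R = 1, 2 or 4. All deaths counted fall after discharge. Relapses are not modelled, because the article gives no rate for them.

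**Step 1: how many die with a zero count.** Expected deaths are 0.12 × 60 = 7.2, which is a ceiling. The others' rate is λ0 = 0.431/(0.88 + 0.12R), and the rate of those who die is λf = Rλ0. With uniform death times, P(no readmission | died) = (1 − e^(−λf))/λf.

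| R | λf | P(zero, given died) | Share of all patients | Of 60 |
|---|---|---|---|---|
| 1 | 0.431 | 0.81 | 0.12 × 0.81 = 9.7% | 5.8 |
| 2 | 0.769 | 0.70 | 0.12 × 0.70 = 8.4% | 5.0 |
| 4 | 1.267 | 0.57 | 0.12 × 0.57 = 6.8% | 4.1 |

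Constant, independent hazards for the two events instead give 9.6% to 9.8%. If the fraction of deaths without readmission is left open at 0.25 to 1, the share is 3% to 12%.

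**Step 2: effect on the comparison.** Take 18% mortality in one arm and 6% in the other (mean 12%), with no true effect on the readmission rate. A frail 18% of patients in each arm has rate λf = Rλ0, with λ0 = 0.431/(0.82 + 0.18R). All of them die in the first arm and one third in the second. A patient who dies is at risk for half the window on average, so the mean counts are:

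- 18% arm: 0.82λ0 + 0.18 × λf/2
- 6% arm: 0.82λ0 + 0.12λf + 0.06 × λf/2

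The standard error (SE) of the difference is √((V1 + V2)/30), where V1 and V2 are the variances of the count in the two arms.

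| R | Mean count, 18% arm | Mean count, 6% arm | Difference | SE | Difference/SE |
|---|---|---|---|---|---|
| 1 | 0.392 | 0.418 | 0.026 | 0.166 | 0.16 |
| 2 | 0.365 | 0.409 | 0.044 | 0.163 | 0.27 |
| 4 | 0.330 | 0.397 | 0.067 | 0.167 | 0.40 |

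The arm with more deaths looks better each time. The constant-hazard calculation gives 0.421 versus 0.450, a difference of 0.029 in the same direction. With equal mortality in the two arms it gives a difference of zero.

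**Step 3: what the alternatives do in the same illustration.** Mean time alive is 1 − 0.18/2 = 0.91 and 1 − 0.06/2 = 0.97 of the window. Dividing the mean counts by these gives the rate per 3 months alive.

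| R | Rate, 18% arm | Rate, 6% arm | Difference | Readmitted or dead, 18% arm | Readmitted or dead, 6% arm |
|---|---|---|---|---|---|
| 1 | 0.431 | 0.431 | 0 | 46.7% | 38.9% |
| 2 | 0.401 | 0.422 | 0.020 | 43.1% | 37.3% |
| 4 | 0.363 | 0.410 | 0.047 | 38.0% | 34.1% |

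The rate removes the shift if those who die are readmitted at the same rate as the others, and only part of it otherwise. The composite does not score a death as a success.

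**The case against.** Several points on the other side have force.

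- **The 12%.** A reader might infer that about 12% of patients die without readmission. The documents do not support that. The 12% is total mortality, including deaths during or after a readmission, and the share without readmission is not given. The figure is also a background one, and this trial limits age to 45 to 75 years and prior-year admissions to at most three, so its mortality may differ.
- **The size.** A reader might infer that the trial is likely to report a false readmission benefit. The numbers do not show that. Even a threefold mortality difference, after at most five sessions, shifts the result by 0.2 to 0.4 standard errors. A shift of that size raises a two-sided 5% false-positive rate to only about 5.3% to 6.9%.
- **Visibility.** Mortality is reported by arm over the same period, so an imbalance would be seen. This stands, but it lets a reader only suspect the distortion. The readmission estimate and its interval would be unchanged.
- **Last value carried forward.** It is tempting to blame this rule. A count taken from the clinical history up to death is complete, so the rule need not apply, and the point adds little.
- **Detail left to a fuller document.** The denominator is indeed not stated, and that every discharged patient is counted is an inference from intention to treat. But the summary measure is stated, and a raw mean over a fixed window is where the problem lies. Restricting it to survivors would condition on an event after randomization and would not cure it.
- **The composite.** A reader might conclude that readmitted-or-dead should replace the count. That is debatable. It drops relapses and repeat admissions and counts deaths that are already a separate outcome. In the illustration its direction follows from the assumed mortality difference. A count of readmissions incurred is also a legitimate measure of resource use. The composite is better as a supportive result.

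**Conclusion.** The point holds as a minor one on a secondary outcome. The stated measure gives the best possible score to a patient who dies after discharge without readmission. Up to 12% of patients may die in the window. Under the assumed uniform death times and Poisson readmissions, about 7% to 10% (4 to 6 of 60) would do so without readmission.

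Bias between arms arises only if mortality or its timing differs, and it then favours the arm with more deaths. The illustrated 0.03 to 0.07 readmissions per patient rests on an assumed 18% versus 6% mortality and on readmissions alone. Relapses would add to the count by an amount the article does not allow one to calculate. Deaths in hospital are outside this point, and neither the primary outcome nor the sample size is affected.

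**What to change.** Under Secondary outcome measures, replace the comparison of raw means by a comparison of relapses and readmissions as a rate per days alive after discharge, up to 3 months, using a count model with log days alive as offset. Report the number of deaths by arm beside the rate.

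Add, as a supportive analysis, the proportion readmitted or dead within 3 months of discharge. Compare it by the risk ratio with 95% confidence interval already planned for dichotomous outcomes, and show both components separately.

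The cost is slightly more analysis work. Readmissions and deaths are already outcomes of the trial; the only other item needed is the date of death, if the form does not already hold it. Sample size and visits do not change. One limit remains: if patients who die also have a higher readmission rate, the rate removes the bias only in part, which is why the composite is shown alongside.

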Several clinical studies using AcuTENS in patients with COPD have recently been published. All studies have used the stimulation of the acupuncture point named Dingchuan (EX-B1), traditionally used to treat dyspnoea. In those studies, a decrease in dyspnoea and an increase in forced expiratory volume in 1 second (FEV 1), β-endorphin level and quality of life have been observed [11–13]. However, these studies have been conducted on patients in stable condition, and little is known about the possible effect of this technique in patients with an AECOPD. Only one case study suggesting possible benefits for shortness of breath besides an increase in the level of oxygen saturation and β-endorphins has been published to date [14], and properly designed randomized placebo-controlled trials are needed to confirm these results.

The objectives of this study are to determine whether the use of AcuTENS at the Dingchuan point (EX-B1) could be beneficial for patients hospitalized for AECOPD by reducing dyspnoea, days of hospitalization, and consumption of regular medication. Moreover, we will assess possible adverse effects of this technique and its effect on mortality and readmissions at 3 months after discharge.

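### The mortality window opens at discharge, so deaths between randomisation and discharge are not counted, and no rule says how they enter length of stay or readmissions

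*Protocol article*

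**What the plan says.** Under Secondary outcome measures, the protocol article defines three outcomes by the moment of discharge.

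- **Mortality:** "Mortality will be assessed by using the ratio of patients who died during the 3-month period after discharge in each group".
- **Length of stay:** "Hospitalization length will be measured by using the number of days from the time of admission until the patient’s discharge". The comparison is by means: "Scores will be compared by using mean differences between groups".
- **Relapse and readmission:** "Mean number of relapses and readmissions during the 3-month period after discharge will be compared between groups".

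The objective at the end of the Background also refers to discharge: "its effect on mortality and readmissions at 3 months after discharge". Statistical methods is looser: "For dichotomous outcomes (such as mortality at 3 months), risk ratio will also be used". It gives no starting point for the 3 months. The test named there for dichotomous outcomes is chi-squared.

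Patients are recruited in the first 48 hours of the stay (Participants) and treated for up to five consecutive days or until they leave hospital (Interventions). The main analysis is by intention to treat, and the only missing-data rule is to carry the last value forward (Statistical methods).

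**The concern.** Randomisation starts the comparison, but the mortality window starts later, at an event that some patients may never reach. A patient who dies on the ward is not in the numerator, although this is the period closest to the intervention. Adverse events do not fill the gap: the evaluator asks the patient after each session about events related to the intervention, which is not a way to record deaths.

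The same patient has no discharge date and no time at risk of readmission. Two codings are open:

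- Death is taken as the end of the stay, with zero readmissions. An early death then looks like a short, uncomplicated stay.
- The patient is left out. The comparison is then among those who left hospital alive, which departs from intention to treat.

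Carrying the last value forward cannot supply a discharge date. Shorter hospital stay is a stated objective and part of the cost argument in the Discussion, so the coding bears on something the trial intends to report.

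**Working it through.** **The plan's own figure.** Sample size gives a difference of 2 Borg points, SD 2.6, α 0.05 (taken as two-sided), β 0.2 and 10% losses. Per arm, n = 2 × (1.960 + 0.842)² × 2.6² / 2² = 26.5, rounded up to 27. Then 27 / 0.9 = 30 per arm, 60 in total. The stated 60 is reproduced and is not in dispute.

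**Is there another place where ward deaths are counted?**

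| Place | What it fixes | Covers randomisation to discharge? |
|---|---|---|
| Secondary outcome measures, mortality | deaths within a period that begins at discharge | No |
| Background, objective | mortality at a time measured from discharge | Not stated |
| Statistical methods | mortality at 3 months, no origin | Not stated |
| Secondary outcome measures, adverse events | patient asked after each session | Not clearly |

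Only the first row defines the outcome, and it excludes these deaths.

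**How many patients?** The documents give no in-hospital death rate, so p is an assumption. Expected number = 60p; chance of at least one = 1 − (1 − p)^60.

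| Assumed p | Expected deaths before discharge | Chance of at least one |
|---|---|---|
| 1% | 0.6 | 45% |
| 2% | 1.2 | 70% |
| 3% | 1.8 | 84% |
| 5% | 3.0 | 95% |

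**Effect on the mortality comparison (constructed examples, 30 per arm).**

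- Four deaths in each arm: true risk ratio (4/30)/(4/30) = 1.0. If 3 of the 4 occur in hospital in arm A and 1 of the 4 in arm B, the definition counts 1 against 3. The ratio is (1/30)/(3/30) = 0.33, or (1/27)/(3/29) = 0.36 with discharged patients as denominator.
- Five deaths against three: true ratio 5/3 = 1.67. If two of the five and none of the three occur in hospital, the definition counts 3 against 3, giving 1.0 (or 1.07 with discharged patients as denominator). An excess disappears.

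**Effect on length of stay, if a death is entered as the end of stay.** Assume death on day 3 and a mean of 8 days otherwise. Each death moves a 30-patient mean by (3 − 8)/30 = −0.17 day; two move it by −0.33 and three by −0.50. With death on day 2 or 3 and a mean of 7 to 10 days, the shift per death runs from (3 − 7)/30 = −0.13 to (2 − 10)/30 = −0.27 day.

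**Effect on readmissions, if zero is entered.** Using the Background's 35%, the arm figure becomes 0.35 × (30 − k)/30: 33.8%, 32.7% and 31.5% for k = 1, 2 and 3 deaths.

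**Choice of test.** If the Background's 12% mortality applied, expected deaths would be 0.12 × 30 = 3.6 per arm, below the usual minimum of 5 per cell for chi-squared.

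**The case against.** The strongest reply is that this is loose wording in a condensed article. The objective and Statistical methods can both be read as vital status at a time point, which would include earlier deaths, and the main analysis is by intention to treat. The figure with the assessment schedule is not available. It stands that the documents do not show an intention to exclude ward deaths. It does not remove the point, because the one sentence that defines the outcome confines it to a period after discharge, and the looser phrases do not override it.

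A reader might go further and infer that length of stay and readmissions are biased in favour of the arm with more deaths. The documents do not support this. They give no coding rule; if the dead are treated as missing, the short-stay mechanism does not operate, and a late ward death lengthens the stay. Where the mechanism does operate, the shifts above are small.

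A reader might also want the share of all deaths that goes uncounted. It cannot be fixed from the documents. At an assumed in-hospital rate of 2% to 6% (1.2 to 3.6 of 60), it is 1.2/8.4 = 14% to 3.6/10.8 = 33% if the 12% (7.2 of 60) covers only later deaths, but 1.2/7.2 = 17% to 3.6/7.2 = 50% if the 12% already includes ward deaths. The Background does not say which. Nor need 12% apply to this sample, which is limited to ages 45 to 75 and excludes several comorbidities.

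Finally, mortality is one of several secondary outcomes in a trial of 60 patients. Calling it the main safety outcome would go beyond the text.

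**Conclusion.** The point holds for mortality as written: deaths from randomisation to discharge are outside the outcome and are not clearly captured elsewhere. With so few events, one or two such deaths can change the risk ratio materially, as the constructed examples show. The number affected, about 0.6 to 3 of 60, rests on an assumed in-hospital rate of 1% to 5%.

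For length of stay and readmissions the point is conditional: the definitions leave ward deaths without a rule, and either obvious coding could distort the comparison, probably modestly. The reservation about chi-squared is secondary and depends on mortality being near the 12% in the Background or lower.

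The issue is confined to secondary outcomes. The primary Borg comparison and the sample size stand.

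**What to change.** - **Mortality.** Define it as death from any cause from randomisation to a fixed time in all randomised patients: for example 90 days after randomisation, or through 3 months after discharge with in-hospital deaths included. Align the objective and Statistical methods with this wording.
- **Length of stay and readmissions.** State that a death before discharge is not scored as a short stay or as readmission-free. For example, rank such deaths worst for length of stay, which the already listed Mann–Whitney test can accommodate, and report deaths alongside readmissions.
- **Test.** Use Fisher's exact test for mortality in place of chi-squared, keeping the risk ratio with its interval.

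The sample size stays at 60 and no visits are added. The cost is a change of wording, probably by amendment, since recruitment was due to start in April 2018. The article names the clinical history as the source for readmissions but names no source for deaths; dates of in-hospital death should be in the same record, and this should be confirmed. The rule should be fixed before any unblinded analysis, because choosing afterwards how deaths count could change the result.
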